### Strategies to improve adherence to interventions {11c}

Teacher adherence to the programme will be assessed by a self-report checklist of completed sessions. The intervention material itself is pre-prepared, so providing it is delivered to the class, adherence has been achieved. Child attendance will be recorded by teachers at T2 as a binary report of whether children attended half or more of the taught sessions, or less than half.

Schools will be randomised to receiving CUES for schools in addition to the usual school curriculum, either now (CUES) or later (WL).

### Relevant concomitant care permitted or prohibited during the trial {11d}

Not applicable. There is no concomitant care, and we are placing no restriction on any school activity in the waitlist condition.

### Provisions for post-trial care {30}

Not applicable. No provision has been made for post-trial care, as we anticipate no need.

### Outcomes {12}

#### Primary outcome

We will use the M&MF [17] total score in vulnerable children at 16 weeks.

This measure comprises 16 items, each rated 0 (best) to 2 (worst), with total scores ranging from 0 to 32. The total score is made up from two subscales — emotional difficulties (M&MF-E, 10 items) and behavioural difficulties (M&MF-B, 6 items) — with children meeting the criterion for being vulnerable based on M&MF-E > 9 and/or M&MF-B > 5. The measure is designed specifically for use in schools to evaluate public health initiatives and has been widely used with children of this age group.

#### Secondary outcomes

##### Vulnerable sub-population

M&MF-E 10-item subscale (M&MF items 1–10) at 16 weeks. Scores range from 0 to 20, with lower scores indicating more positive outcomes (clinical cut-off > 9).M&MF-B 6-item subscale (M&MF items 11–16) at 16 weeks. Scores range from 0 to 12, with lower scores indicating more positive outcomes (clinical cut-off > 5).Child Outcome Rating Scale (CORS) [18] 4-item total scale at 16 weeks. This scale is designed to measure wellbeing and distress, with each item rated 0 (worst) to 10 (best) with scores below 32 considered to represent clinical levels of distress/poor wellbeing.Child workbook 7-item wellbeing rating scores at 16 weeks. Each item is rated from 0 (worst) to 10 (best), with total scores ranging from 0 to 70.Child workbook 8-item cognitive rating scores at 16 weeks. Each item is rated from 0 to 1, with one item rated from 0 to 2. Total scores range from 0 to 9.

##### Whole school population

M&MF-E 10-item subscale (M&MF items 1–10) at 16 weeks.M&MF-B 6-item subscale (M&MF items 11–16) at 16 weeks.CORS 4-item total scale at 16 weeks.Child workbook 7-item wellbeing rating scores at 16 weeks.Child workbook 8-item cognitive rating scores at 16 weeks.Teacher ratings of whole class behaviour (ratings I–II) at 16 weeks. This involves estimates of the proportion of the class displaying positive behaviours, rated as the total number of children within the class who ‘often’ or ‘sometimes’ display these behaviours.Teacher 4-item coping scale at 16 weeks. Each item is rated from 0 (worst) to 4 (best), with total scores ranging from 0 to 16. This scale is designed to indicate how well the teacher feels they are able to manage emotional upset experienced by children within the classroom.

#### Exploratory outcomes (not formally assessed)

*Teacher adherence* data will be collected from a self-report checklist.*Child attendance* data will be collected from the class teacher.

### Participant timeline {13}

The participant timeline is shown in Table 1.

### Sample size {14}

In our feasibility trial [19], we found an effect size of 0.2. Assuming a type-1 error = 0.05 (two-sided test) with 90% power and an intraclass coefficient (ICC) of 0.025, a total of 68 schools are needed to be included in the analysis population, each with 25 vulnerable children. After accounting for a loss to follow-up at 5% of schools, and then a loss of 15% of vulnerable children, we will randomise 74 schools (1:1) to enrol 2220 vulnerable children.

In typical schools, there are approximately 75 Year 4 children, of which 40% are vulnerable, thus 30 vulnerable children per school. Approximately 5550 children will be enrolled in total, including 2220 vulnerable and 3330 non-vulnerable.

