#### Children

All children will be invited to attend CUES sessions and complete outcomes, unless parents or the children themselves request not to participate. This is because it is important that the parental opt-out process for research use of data does not result in children feeling excluded or stigmatised. Children will give assent for the use of their measures for research. This will be given as privately as possible, again to avoid any stigma. We will only use data when parents have not opted out and children have assented.

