## Discussion

The CUES for schools study will evaluate an interactive digital platform designed for teacher-facilitated delivery in primary school children. Trial procedures have been shown to be feasible, and in excess of 6000 children have received an expert-delivered version of the programme as part of local service delivery ([name] et al., personal communication).

This study will extend recruitment from inner London to outer London and the home counties. Feasibility study uptake was 11 of 36 eligible schools (30%) with 14 expressing interest. As we are recruiting across nearly 40 boroughs/counties, each with 40–80 eligible schools, we do not anticipate difficulty recruiting to our target of 74 schools and can increase this if insufficient numbers of vulnerable children are enrolled. No teacher declined participation. Our feasibility study employed a parental consent and child assent procedure: 8% of parents and 13% of children declined consent; just over 40% of parents and just over 75% of children returned a form and agreed participation. We anticipate higher parental return rates using an opt-out procedure. Parental and child requests to withdraw from delivery of the programme were low (*n* = 2), similar to in-service delivery, and child and teacher feedback in-service was consistent with acceptability, and safety, with no adverse events reported in the feasibility study, or during in-service delivery [5, 19]. Over 80% of children completing baseline assessments were retained in the feasibility study at follow-up.

Teachers varied in the timeliness of programme delivery in the feasibility study: we have implemented a weekly adherence check for this study to facilitate delivery within the 16-week window.

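### The enrolment figures of 30 vulnerable children per school, 2220 vulnerable and 5550 in all count the whole Year 4 roll as participating, against the protocol's own assent rule and feasibility refusal rates

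*Protocol article*

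**What the plan says.** All of the sample-size inputs are in Sample size {14}. The effect is taken from earlier work: "In our feasibility trial [19], we found an effect size of 0.2". The error rates and clustering follow: "Assuming a type-1 error = 0.05 (two-sided test) with 90% power and an intraclass coefficient (ICC) of 0.025". The analysis requirement is that "a total of 68 schools are needed to be included in the analysis population, each with 25 vulnerable children". The allowance for losses reads: "After accounting for a loss to follow-up at 5% of schools, and then a loss of 15% of vulnerable children". This leads to 74 randomised schools and 2220 enrolled vulnerable children. The supply per school is given as: "In typical schools, there are approximately 75 Year 4 children, of which 40% are vulnerable, thus 30 vulnerable children per school". The section closes with a total of about 5550 children enrolled, 2220 of them vulnerable and 3330 not.

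Three other places bear on participation:

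- Recruitment {15}, Children: "We will only use data when parents have not opted out and children have assented".
- Discussion, on the feasibility study: "8% of parents and 13% of children declined consent; just over 40% of parents and just over 75% of children returned a form". The same paragraph expects parental return to improve under opt-out, and says the number of schools can be raised if too few vulnerable children are enrolled.
- Discussion, final paragraph: the expectation is to enrol most of the children in each school, not all of them.

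**The concern.** The calculation goes straight from the year-group roll to the enrolled sample with no step for refusal. The only reductions are the 5% of schools and the 15% of vulnerable children. Both are follow-up losses, and the second is consumed between 30 enrolled and 25 analysed. Nothing is left to absorb children who do not assent or whose parents opt out, although the protocol makes both a condition of using data.

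Two stated figures are affected. The enrolment target would be missed even with all 74 schools on board and no school lost. The 90% power rests on 25 analysed vulnerable children per school, a cluster size that the stated roll, prevalence and losses reach only with full participation. A team monitoring recruitment against 2220 would then see a shortfall that could have been foreseen from the protocol itself.

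**Working it through.** **Reproducing the plan's figure.** Inputs from Sample size {14}: standardised effect 0.2, two-sided 5%, power 90%, ICC 0.025, 25 analysed per school.

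- Per arm without clustering: 2 × (1.960 + 1.282)² / 0.2² = 525.4, so 526.
- Design effect: 1 + (25 − 1) × 0.025 = 1.6.
- Schools per arm: 526 × 1.6 / 25 = 33.7, so 34, or 68 in total. This matches.
- Loss of schools: 68 / 0.95 = 71.6, so 72. The plan takes 74, which leaves two spare.
- Loss of children: 25 / 0.85 = 29.4, so 30 per school.
- Totals: 74 × 30 = 2220 and 74 × 75 = 5550. Both hold only if everyone on the roll takes part.

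**Adding a participation rate p.** The Discussion gives 8% parental and 13% child refusal in the feasibility study. Enrolled vulnerable per school = 30p; analysed per school m = 30p × 0.85; schools retained = 74 × 0.95 = 70.3. Effective number per arm = (70.3 × m / 2) / (1 + (m − 1) × 0.025), and power = Φ(0.2 × √(effective number / 2) − 1.960).

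| Refusal assumed | p | Vulnerable per school | Vulnerable in 74 schools | All children (5550p) | m | Effective n per arm | Power |
|---|---|---|---|---|---|---|---|
| None (as planned) | 1.00 | 30 | 2220 | 5550 | 25.5 | 555.9 | 91.5% |
| Parents 8% only | 0.92 | 27.6 | 2042 | 5106 | 23.5 | 528.1 | 90.1% |
| Children 13% only | 0.87 | 26.1 | 1931 | about 4830 | 22.2 | 509.8 | 89.1% |
| Both, 0.92 × 0.87 | 0.80 | 24.0 | 1777 | about 4440 | 20.4 | 483.0 | 87.5% |

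Worked line for both refusals: 70.3 × 20.41 / 2 = 717.4; design effect 1 + 19.41 × 0.025 = 1.485; 717.4 / 1.485 = 483.0; 0.2 × √241.5 = 3.108; Φ(1.148) = 0.875.

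The product 0.92 × 0.87 treats the two refusals as independent. If the parental refusals fell entirely among the children who refuse, p would be 0.87, the third row. If they never overlapped, p would be 0.79: 23.7 per school, 1754 in total, 20.1 analysed, power 87.2%. The degree of overlap therefore hardly moves the lower end.

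**Baseline adjustment.** The primary model adjusts for baseline score, and the calculation takes no credit for it. Suppose the baseline correlation is 0.5 and acts on the child-level variance only (an assumption; the protocol gives no figure). The variance of the difference is then 4 × (0.025 + 0.975 × 0.75 / m) / 70.3. For m = 22.2 the ratio of effect to standard error is 3.48 and power is 93.6%; for m = 20.4 they are 3.40 and 92.5%.

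**The case against.** The strongest reply is that the refusal rates belong to another procedure. The feasibility study asked parents for consent; this trial offers them an opt-out, and no opt-out rate is given. That stands, so the figures for both refusals are conditional. It does not dispose of the point, because children still have to assent. The 13% is the only child refusal figure in the document, and on its own it gives 1931 vulnerable children. Even the 8% alone gives 2042, although power then stays at 90%.

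Second, the Discussion allows for adding schools, with nearly 40 boroughs or counties to draw on. This is a real remedy, and it means the trial is not bound to fall short. However, Sample size {14} does not build it in and no trigger is stated.

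Third, the 40% may be cautious, since the Background reports that nearly half of London children aged 7 to 10 were vulnerable. At 48% (an assumption) both refusals would give 75 × 0.48 × 0.80 = 28.8 per school and 90.9% power. This shows how far the power result depends on that input. But 40% is what the plan fixed, and 2220 rests on it.

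Fourth, the planned baseline adjustment probably recovers the lost power, as shown in the working. It does nothing for the enrolment count.

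**Conclusion.** The point holds as an inconsistency in the stated figures. The 30, 2220 and 5550 describe the year-group roll, not the children whose data can be used. On the feasibility refusal rates, 74 schools would give about 24 to 26 vulnerable children per school, about 1780 to 1930 vulnerable and about 4440 to 4830 children in all, which is 13 to 20% below the stated totals. Power on the stated inputs would be about 87 to 89%, one to three points under 90%. This rests on the feasibility rates carrying over, on 40% vulnerable, and on the planned 5% and 15% losses.

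A reader might infer more than the document supports:

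- *About 21 per school and 84% power.* This would apply the 75% child agreement figure. That figure also leaves out children who returned no form, so it is not a refusal rate.
- *The 15% loss is too optimistic.* The Discussion says: "Over 80% of children completing baseline assessments were retained in the feasibility study at follow-up". That is a lower bound and is compatible with 85%. The primary analysis also keeps any child with at least one follow-up.
- *A further loss from unequal school sizes.* Balancing on school size does not show how much size varies, and the protocol gives no coefficient of variation.
- *The trial is underpowered and needs more schools.* The gap is small, the adjusted primary analysis may close it, and the plan already allows schools to be added.

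**What to change.** In Sample size {14}, insert an explicit expected participation rate between the Year 4 roll and the enrolled sample, saying whether it comes from the feasibility study or is an assumption under opt-out. Then restate expected enrolment; at 8% and 13% refusal this is about 4440 children, of whom about 1780 are vulnerable. Give the power at the resulting analysed cluster size. If wished, show separately the power with the planned baseline adjustment, with the assumed correlation stated.

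The cost is one reworded paragraph and less favourable headline figures. Neither the design nor the number of schools has to change.

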### Recruitment {15}

#### Schools

We will recruit schools through local authority listings, contacting all schools in inner and outer London to inform them of the study and invite an expression of interest before formally liaising with SLTs and teachers for consent. Each school will be approached for SLT consent, with discussion with the research team as needed. Teachers will be approached by their SLT to discuss participation. However, as the SLT is also their management, they will each have a separate discussion with the research team to ensure they have the opportunity to decline participation should they wish to. SLTs will agree, as part of their consent on behalf of the school, to teachers being free to decide to participate or otherwise without this compromising their relationship with their school in any way.

#### Parents

Once SLT and teacher consent are secured, letters will be sent to all parents in the target year group explaining the study and offering the opportunity to opt out of CUES sessions and/or assessments by liaising with the school, or the use of child-reported outcome measures for a research purpose, by liaising with the research team. If parents wish, they can request a discussion with the research team directly using the email provided in the information sheet, or via the school office or teacher.

#### Children

All children will be invited to attend CUES sessions and complete outcomes, unless parents or the children themselves request not to participate. This is because it is important that the parental opt-out process for research use of data does not result in children feeling excluded or stigmatised. Children will give assent for the use of their measures for research. This will be given as privately as possible, again to avoid any stigma. We will only use data when parents have not opted out and children have assented.

## Assignment of interventions: allocation

### Sequence generation {16a}

Randomisation will be carried out following SLT/teacher consent, the sending of parental information sheets, and when teachers and children have completed baseline assessment and prior to the start of the intervention. Cluster randomisation will be managed by an unblinded statistician. We will randomise using covariate-constrained cluster randomisation balancing on school deprivation and school size [20].

### Concealment mechanism {16b}

Randomisation will be managed by the unblinded study statistician. Cluster characteristics needed by the statistician in order to perform the randomisation will be sent through by the trial manager once the school is confirmed as taking part in the study. Allocations will then be sent to the trial manager once all baseline data has been collected from the participants.

### Implementation {16c}

Schools will be randomised once baseline assessments are completed. The member of the study team overseeing the collecting and return of the baseline measures will alert the unblinded study statistician who will send the allocation to the research team. This person will communicate with the school and ensure that appropriate steps are initiated (i.e. teacher induction and onboarding so they can deliver CUES for intervention schools).

## Assignment of interventions: blinding

### Who will be blinded {17a}

Outcome measures are completed by the participants and teachers who cannot be blind to allocation. Researchers facilitating outcome completion will not be blind to allocation, as schools tend to decorate the classroom with CUES materials (e.g. children’s drawings) during delivery. Data processing, however, will be conducted blind to allocation. The senior statistician on the study will remain blind throughout and only ever see pooled data. The trial statistician will remain fully blind until the statistical analysis plan (SAP) is approved by the Trial Steering Committee (TSC) independent statistician, then they will be partially blinded (aware of arms coded A and B).

### Procedure for unblinding if needed {17b}

Not applicable as this is a low-risk study there is no need for an unblinding procedure.

## Data collection and management

### Plans for assessment and collection of outcomes {18a}

Outcome measures (child emotional/behavioural problems, child wellbeing, teacher-rated class behaviour) will be completed by children and teachers at T0, T1 (primary outcome only), and T2, on paper, with support from a research worker online or in-person as required. Measures will be completed as a group in the classroom. Assessments should occur within a 6-week window of their calendar date (up to 2 weeks earlier or up to four weeks later), counted from the day of randomisation. Assessments will be collected by teachers and returned securely by courier to the research team.

### Plans to promote participant retention and complete follow-up {18b}

None.

### Data management {19}

Data will be collected in paper format and will be entered onto and managed using REDCap electronic data capture tools hosted at King’s College, London [21, 22]. REDCap (Research Electronic Data Capture) is a secure, web-based software platform designed to support data capture for research studies, providing (1) an intuitive interface for validated data capture; (2) audit trails for tracking data manipulation and export procedures; (3) automated export procedures for seamless data downloads to common statistical packages; and (4) procedures for data integration and interoperability with external sources.

Teacher adherence, schoolchild attendance, and school reports of usual curriculum delivery will be held in a separate Microsoft Excel [23] database by unblinded members of the research team. Paper forms will be stored securely by the research team until the end of the study (January 2024).

Separate databases will be created for school-level data, class/teacher-level data, child-level data, and allocation. The database will be designed to only accept within range responses. Range and value checks and spot checks against paper copies will be employed to check 20% of entered data.

### Confidentiality {27}

#### Security and backup of data

Data will be stored on password-protected systems in the hosting trust and academic organisations (South London & Maudsley National Health Service Foundation Trust, SLaM and KCL). The allocation database will be accessible only to the lead research worker (who will not conduct post-baseline assessments) and the Chief Investigator (DP) until the study is completed. Outcome data processing will be carried out by researchers who do not have access to allocation, intervention or feedback data. Once all data is entered, cleaned and checked, blind to allocation, the database will be locked. A final database will be returned to the statistician, who will combine with allocation data for analysis. The Chief Investigator will act as custodian for the trial data. The following guidelines will be strictly adhered to:

Child/teacher data will be pseudonymised for the duration of the study and fully anonymised at the end of the study. The fully anonymised data will be kept indefinitely. Fully identifiable personal details will be kept for parents opting out on paper in a locked filing cabinet in a locked or occupied office and on university servers (as responses are returned using a university-based system) until the end of data collection for the study (March 2023).

#### End of the trial

The end of the trial will be defined as a database hard lock. This will be defined as the removal of editing user access for those entering data into the REDCap database.

### Plans for collection, laboratory evaluation and storage of biological specimens for genetic or molecular analysis in this trial/future use {33}

Not applicable. There are no biological specimens collected in this study.

## Statistical methods

### Statistical methods for primary and secondary outcomes {20a}

Prior to the database lock a statistical analysis plan (SAP) will be developed following King’s Clinical Trials Unit (KCTU) Standard Operating procedures (KCTU ST:02 — developing a statistical analysis plan) and approved by the trial team and the independent TSC chair statistician.

Briefly, all statistical analyses will adopt an intention-to-treat principle (ITT) whereby all schoolchildren will be analysed in accordance to the condition in which they were randomised, with this being a modified ITT for the primary outcome to allow for the inclusion of only the vulnerable sub-sample. All analyses will be conducted after data collection has been completed and pre-processed, the SAP has been signed off and the database has been locked. All variables will first be summarised using descriptive statistics (e.g. means and SDs for normally distributed continuous variables, and median and interquartile ranges skewed continuous data), prior to inferential analyses, and M&MF descriptives will be further sub-divided to confirm the proportion of children meeting the criteria for vulnerability at each timepoint.

